**Discharge**

N3. In the past 6 months, have you had abnormal or unusual discharge from the vagina (women)/penis(men)? Please do not include discharge during sexual intercourse.

_____ 0. No  *Skip to N7*

_____ 1. Yes

*_____-1. Don’t know*  *Skip to N7*

*_____-2. Refused*  *Skip to N7*

N4. Did you receive treatment for the discharge?

_____ 0. No *Skip to N6*

_____ 1. Yes

*_____-1. Don’t know* *Skip to N6*

*_____-2. Refused*  *Skip to N6*

N5. Where did you receive this treatment? [*Tick all that apply].*

_____ 1. HIV clinic

_____ 2. STI clinic

_____ 3. Out patient day clinic

_____ 4. Pharmacy

_____ 5. Traditional healer not in health care clinics

_____ 6. Other (specify) _______________________

*_____-1. Don’t know*

*_____-2. Refused*

N6. Did your sex partner(s) get treated for discharge?

_____ 0. No

_____ 1. Yes

*_____-1. Don’t know*

*_____-2. Refused*

**Genital sores**

N7. In the past 6 months, have you had any sores in your genital area?

_____ 0. No  *Skip to N11 if* ***FEMALE*** *or P1m if* ***MALE***

_____ 1. Yes

*_____-1. Don’t know*  *Skip to N11 if* ***FEMALE*** *or P1m if* ***MALE***

*_____-2. Refused*  *Skip to N11 if* ***FEMALE*** *or P1m if* ***MALE***

N8. Did you receive treatment for the sores in your genital area?

_____ 0. No  *Skip to N10*

_____ 1. Yes

*_____-1. Don’t know*  *Skip to N10*

*_____-2. Refused*  *Skip to N10*

N9. Where did you receive this treatment? [*Tick all that apply].*

_____ 1. HIV clinic

_____ 2. STI clinic

_____ 3. Out patient day clinic

_____ 4. Pharmacy

_____ 5. Traditional healer not in health care clinics

_____ 6. Other (specify)____________________

*_____-1. Don’t know*

*_____-2. Refused*

N10. Did your sex partner(s) get treated for genital sores?

_____ 0. No

_____ 1. Yes

*_____-1. Don’t know*

*_____-2. Refused*

*Males skip to P1m in next section*

**FOR FEMALES ONLY**

**Lower Abdominal Pain:**

N11. In the past 6 months, have you had pain in your lower abdomen?

_____ 0. No  *Skip to the beginning of the* **Family Planning** *section*

_____ 1. Yes

*_____-1. Don’t know*  *Skip to the beginning of the* **Family Planning** *section*

*_____-2. Refused*  *Skip to the beginning of the* **Family Planning** *section*

N12. Did your health care provider treat this lower abdominal pain as a sexually transmitted infection?

_____ 0. No  *Skip to the beginning of the* **Family Planning** *section*

_____ 1. Yes

*_____-1. Don’t know*  *Skip to the beginning of the* **Family Planning** *section*

*_____-2. Refused*  *Skip to the beginning of the* **Family Planning** *section*

N13. Did you receive treatment for this lower abdominal pain?

_____ 0. No  *Skip to N15*

_____ 1. Yes

*_____-1. Don’t know*  *Skip to N15*

*_____-2. Refused*  *Skip to N15*

N14. Where did you receive this treatment? [*Tick all that apply].*

_____ 1. HIV clinic

_____ 2. STI clinic

_____ 3. Out patient day clinic

_____ 4. Pharmacy

_____ 5. Traditional healer not in health care clinics

_____ 6. Other (specify) ____________________

*_____-1. Don’t know*

*_____-2. Refused*

N15. Did your sex partner(s) get treated for a sexually transmitted infection?

_____ 0. No

_____ 1. Yes

*_____-1. Don’t know*

*_____-2. Refused*

**Family Planning**

| ***Interviewer reads:*** *“*Now I am going to ask you some questions about pregnancy, family planning, and your desire for children.” |
| --- |

**FOR MALES: GO TO QUESTION P1m ON PAGE 38**

**FOR FEMALES ONLY**

P1f. Has anyone in this HIV clinic ever spoken with you about contraceptives or family planning?

_____ 0. No *Skip to P2f*

_____ 1. Yes

*_____-1. Don’t know*

*_____-2. Refused*

P1fa. Which of the following staff at this HIV clinic have ever discussed contraceptives or family planning with you?

_____ 1. Health Care Provider (e.g, Clinical Officer, Doctor)

_____ 2. Nurse

_____ 3. Counselor

_____ 4. Pharmacist

_____ 5. Other (specify) ____________________

*_____-1. Don’t know*

*_____-2. Refused*

P2f. Are you pregnant now?

_____ 0. No

_____ 1. Yes  *Skip to P11f*

*_____-1. Don’t know*

*_____-2. Refused*

P3f. Do you want to get pregnant in the next 6 months?

_____ 0. No

_____ 1. Yes

*_____-1. Don’t know*

*_____-2. Refused*

P4f. Does your spouse or main sex partner want you to get pregnant in the next 6 months?

_____ 0. No

_____ 1. Yes

_____ 2. Don’t have a spouse or main sex partner

*_____-1. Don’t know*

*_____-2. Refused*

P5f. Have you ever used any method to avoid getting pregnant?

_____ 0. No

_____ 1. Yes

*_____-1. Don’t know*

*_____-2. Refused*

P6f. Are you currently using any of these methods to avoid getting pregnant?

|  | **No** | **Yes** | *Don’t know* | *Refused* |
| --- | --- | --- | --- | --- |
| a. Pill | 0 | 1 | -1 | -2 |
| b. IUD (Intra-Uterine Device) | 0 | 1 | -1 | -2 |
| c. Injectable | 0 | 1 | -1 | -2 |
| d. Implants | 0 | 1 | -1 | -2 |
| e. Condom | 0 | 1 | -1 | -2 |
| f. Diaphragm | 0 | 1 | -1 | -2 |
| g. Foam/jelly | 0 | 1 | -1 | -2 |
| h. Lactational amenorrhea | 0 | 1 | -1 | -2 |
| i. Rhythm Method | 0 | 1 | -1 | -2 |
| j. Withdrawl | 0 | 1 | -1 | -2 |
| k. Female Sterilization | 0 | 1 | -1 | -2 |
| l. Male Sterilization | 0 | 1 | -1 | -2 |
| m. Other (Specify) ______________________ | 0 | 1 | -1 | -2 |

 **If NO to ALL of above, then ask P7f. Otherwise Skip** **P8f.**

P7f. I am going to read you some reasons people sometimes give for not using any method to avoid getting pregnant. For each of these, please tell me if this is a reason why you are not using any method.

|  | **No** | **Yes** | *Don’t know* | *Refused* |
| --- | --- | --- | --- | --- |
| a. I want to have children | 0 | 1 | -1 | -2 |
| b. My partner or I cannot get pregnant | 0 | 1 | -1 | -2 |
| c. I do not like the side effects of contraceptives | 0 | 1 | -1 | -2 |
| d. Contraceptives are inconvenient | 0 | 1 | -1 | -2 |
| e. I do not like the contraceptive methods available to me | 0 | 1 | -1 | -2 |
| f. Contraceptives are too hard for me to get | 0 | 1 | -1 | -2 |
| g. My religion does not allow me to use contraceptives | 0 | 1 | -1 | -2 |
| h. Contraceptives cost too much | 0 | 1 | -1 | -2 |
| i. My partner opposes using contraceptives | 0 | 1 | -1 | -2 |
| j. Contraceptives have never been offered to me | 0 | 1 | -1 | -2 |
| k. I do not know enough about contraceptives to know what to use | 0 | 1 | -1 | -2 |
| l. I just have not thought about using contraceptives | 0 | 1 | -1 | -2 |
| m. Other (Specify) _____________________________ | 0 | 1 | -1 | -2 |

*[ After answering, Skip to P13f]*

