**Hypotheses**

Project hypotheses focus on the effectiveness of the prevention intervention package on behavioral outcomes, biologic outcomes, and delivery of services in the HIV care and treatment settings. Intervention clinics will integrate the HIV prevention intervention package into routine care of HIV-positive patients; comparison clinics will provide standard of care to HIV-positive patients.

Compared to participants attending comparison HIV clinics, participants at intervention clinics will be more likely over a 12-month period to report or show a(n):

Behavioral

- Decrease in unprotected vaginal and anal sex
- Decrease in number of sex partners
- Increase in number of sex partner(s) getting an HIV test
- Increase in disclosure of HIV status to sex partner(s)
- Decrease in alcohol use
- Increase in adherence to HIV antiretroviral medications

Biologic

- Decrease in unintended pregnancy or partner pregnancy
- Decrease in STIs (i.e., urethral discharge)

Service Delivery

Compared to the comparison clinics, the intervention clinics will:

- Provide more family planning counseling (e.g., safer pregnancy) and services (e.g., contraception) to HIV-positive women and their partners

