**Participant exclusion criteria**

Clinic patients

- Younger than 18 years of age
- Not sexually active within the last three months
- Planning to move from the vicinity of the clinic within one year
- Not enrolled in the HIV clinic and/or have not been seen for at least two clinic visits
- Cannot provide informed consent
- Patients who are acutely ill or are determined by clinical staff to be too ill to participate
- Spouses or identified partners of participating patients
- Pregnant women and male partners of pregnant women, as family planning counseling and unintended pregnancy are some of the primary study outcomes
- Not able to complete interview in one of the languages in the inclusion criteria
- Participated in pilot study

Health care providers and lay counselors

- Younger than 18 years of age
- Not fluent/literate in the language selected for the project training
- Planning to leave the clinic within one year
- Not willing to complete project questions
- Do not agree to be observed during patient visits

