Project enrollment will occur over of a 2-3 month period at both intervention and comparison clinics. Following completion of the baseline data collection, the intervention will be implemented at the intervention clinics. Because of the baseline data collection period, the 6-month follow-up will be scheduled for a time estimated to be 6-months after the intervention is integrated into the clinic, so that all intervention clinic participants will have an opportunity to be exposed to the intervention following staff training and implementation. To make the intervention and comparison clinic project procedures as similar as possible, the intervention and comparison clinic 6-month follow-up interviews will occur during the same time period. The same battery of questionnaires will be administered to participants at the 6- and 12-month follow-up interviews, with the exception of some of the sociodemographic questions and items asking about whether something had “ever” happened. At each follow up interview, participants will be offered a soda or other drink and reimbursed for travel costs to the clinic upon completion of the interviews.

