**Write up to three method(s) from P6f:**

**Do not include female sterilization or male sterilization.**

|  | Method 1  ___ *-1. Don’t know*  ___ *-2. Refuse* | Method 2  ___ *-1. Don’t know*  ___ *-2. Refuse* | Method 3  ___ *-1. Don’t know*  ___ *-2. Refuse* |
| --- | --- | --- | --- |
| P8f. The last time you got *[insert method here]* who prescribed it to you or gave it to you?  SKIP THIS QUESTION IF METHOD IS LACTATIONAL AMENORRHEA, RHYTHM METHOD, OR WITHDRAWL | ___ 1. Someone in this  clinic  ___ 2. Someone in another  part of this health  facility  ___ 3. A provider at  another health  facility  ___ 4. Got method without  a prescription  ___ 5. Other source  (specify)  ________________  ___ *-1. Don’t know*  ___ *-2. Refused* | ___ 1. Someone in this  clinic  ___ 2. Someone in another  part of this health  facility  ___ 3. A provider at  another health  facility  ___ 4. Got method without  a prescription  ___ 5. Other source  (specify)  ________________  ___ *-1. Don’t know*  ___ *-2. Refused* | ___ 1. Someone in this  clinic  ___ 2. Someone in another  part of this health  facility  ___ 3. A provider at  another health  facility  ___ 4. Got method without  a prescription  ___ 5. Other source  (specify)  ________________  ___ *-1. Don’t know*  ___ *-2. Refused* |
| P9f. For how long have you been using *[insert method here]* now without stopping? | ________ [# of months]  ________ [# of years]  ___ *-1. Don’t know*  ___ *-2. Refused* | ________ [# of months]  ________ [# of years]  ___ *-1. Don’t know*  ___ *-2. Refused* | ________ [# of months]  ________ [# of years]  ___ *-1. Don’t know*  ___ *-2. Refused* |
| P10f. Does your spouse or main sex partner know that you are using this method of contraception? | _____ 0. No  _____ 1. Yes  _____ 2. Don’t have a spouse or main sex partner  ___ *-1. Don’t know*  ___ *-2. Refused* | _____ 0. No  _____ 1. Yes  _____ 2. Don’t have a spouse or main sex partner  ___ *-1. Don’t know*  ___ *-2. Refused* | _____ 0. No  _____ 1. Yes  _____ 2. Don’t have a spouse or main sex partner  ___ *-1. Don’t know*  ___ *-2. Refused* |

*[After answering, skip to P13f]*

P11f. How many months pregnant are you?

__________ # months pregnant

*_____-1. Don’t know*

*_____-2. Refused*

P12f. At the time you became pregnant, did you want to become pregnant *then*, did you want to wait until *later*, or did you *not want* to have any (more) children?

_____ 1. Then

_____ 2. Later

_____ 3. Not at all

*_____-1. Don’t know*

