**FOR MALES ONLY**

| ***Interviewer reads:***“Now I am going to ask you questions about pregnancy, family planning, and your desire for children with your main partner.” |
| --- |

P1m. Has anyone in this HIV clinic ever spoken with you about contraceptives or family planning?

_____ 0. No *Skip to P2m*

_____ 1. Yes

*_____-1. Don’t know*

*_____-2. Refused*

P1ma. Which of the following staff at this HIV clinic have ever discussed contraceptives or family planning with you?

_____ 1. Health Care Provider (e.g, Clinical Officer, Doctor)

_____ 2. Nurse

_____ 3. Counselor

_____ 4. Pharmacist

_____ 5. Other (specify) ____________________

*_____-1. Don’t know*

*_____-2. Refused*

P2m. Is the person you consider to be your spouse or main partner currently pregnant?

_____ 0. No

_____ 1. Yes  *Skip to P8m*

_____ 2. No main partner  *Skip to Q1 in next section*

*_____-1. Don’t know*

*_____-2. Refused*

P3m. Do you want her to get pregnant in the next 6 months?

_____ 0. No

_____ 1. Yes

*_____-1. Don’t know*

*_____-2. Refused*

P4m. Does your spouse or main partner want to get pregnant in the next 6 months?

_____ 0. No

_____ 1. Yes

*_____-1. Don’t know*

*_____-2. Refused*

P5m. Have you ever used any method to avoid getting your spouse or partner(s) pregnant?

_____ 0. No  *Skip to P7m*

_____ 1. Yes

*_____-1. Don’t know*

*_____-2. Refused*

P6m. Are you, your spouse, or your main sex partner currently using any of these methods to avoid getting pregnant?

|  | **No** | **Yes** | *Don’t know* | *Refused* |
| --- | --- | --- | --- | --- |
| a. Pill | 0 | 1 | *-1* | *-2* |
| b. IUD (Intra-Uterine Device) | 0 | 1 | *-1* | *-2* |
| c. Injectable | 0 | 1 | *-1* | *-2* |
| d. Implants | 0 | 1 | *-1* | *-2* |
| e. Condom | 0 | 1 | *-1* | *-2* |
| f. Diaphragm | 0 | 1 | *-1* | *-2* |
| g. Foam/jelly | 0 | 1 | *-1* | *-2* |
| h. Lactational amenorrhea | 0 | 1 | *-1* | *-2* |
| i. Rhythm Method | 0 | 1 | *-1* | *-2* |
| j. Withdrawl | 0 | 1 | *-1* | *-2* |
| k. Female Sterilization | 0 | 1 | *-1* | *-2* |
| l. Male Sterilization | 0 | 1 | *-1* | *-2* |
| m. Other (Specify) ______________________ | 0 | 1 | *-1* | *-2* |

 **If NO to ALL of above, then ask P7m. Otherwise Skip** **P10m.**

P7m. I am going to read you some reasons people sometimes give for not using any method to avoid getting pregnant. For each of these, please tell me if this is a reason why you and your partner are not using any method.

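### Whether a pregnancy was intended is recorded only if it is current on the interview day, although unintended pregnancy over 12 months is a listed outcome

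*Protocol*

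**What the plan says.** The Hypotheses section of the protocol states that "participants at intervention clinics will be more likely over a 12-month period to report or show" a set of changes, one of which is "Decrease in unintended pregnancy or partner pregnancy". The exclusion criteria rule out women who are pregnant, and men whose partners are, because "family planning counseling and unintended pregnancy are some of the primary study outcomes". The Variables section also lists unintended pregnancies among the primary outcome variables.

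The measurement is in Appendix H, Family Planning:
- Women are asked "P2f. Are you pregnant now". A Yes leads to months pregnant (P11f) and then to "P12f. At the time you became pregnant, did you want to become pregnant" at that time, later, or not at all.
- Men are asked "P2m. Is the person you consider to be your spouse or main partner currently pregnant". A Yes leads to P8m and P9m, the matching items.

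For follow-up, the Data collection section says "The same battery of questionnaires will be administered to participants at the 6- and 12-month follow-up interviews". The only exceptions are some sociodemographic items and items on whether something had ever happened.

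The protocol also names chart review as a source of pregnancy information (Study instruments). Appendix P, item 8, has a pregnancy entry for each dated appointment and a delivery date, in a block for females only.

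**The concern.** The outcome is new unintended pregnancy during follow-up. The only item that establishes whether a pregnancy was unintended is conditional on being pregnant on the interview day. A pregnancy that starts and ends between two interviews cannot be classified from the interview. For a man's partner it is not recorded at all.

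Other topics in the same questionnaire have a look-back window: discharge, genital sores, sex exchange, violence and missed medication over 6 months, and sex acts over 90 days. Pregnancy has none.

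At stake are the completeness of a listed outcome and, if the share of pregnancies ending early differs between arms, the fairness of the comparison. No analysis can recover an answer that was never asked for.

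**Working it through.** **1. Routing.** In Appendix H every path from No at P2f passes P6f and then P7f or P8f-P10f, and rejoins at P13f. Every path from No at P2m rejoins at P10m. So P12f and P9m are reached only after a Yes. No item asks about a pregnancy since the last interview.

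**2. Spacing.** Study timeline windows: January-February 2009, September-October 2009, April-May 2010. Midpoints: 30 January 2009, 1 October 2009, 1 May 2010. At 30.44 days per month:
- baseline to 6-month interview: 244 days, 8.0 months (window extremes 6.1-10.0)
- 6- to 12-month interview: 212 days, 7.0 months (5.0-8.9)
- baseline to 12-month interview: 15.0 months (13.0-16.9)

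**3. What the two interviews catch.** Assumptions not in the protocol: conceptions spread evenly from baseline to the last interview; pregnancy recognised r = 1 to 1.5 months after conception; duration d from 2 to 8.75 months (term); everyone interviewed at the midpoints. Each interview catches conceptions between d and r months earlier, a window of d - r. While the windows do not overlap,

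share missed = 1 - 2(d - r) / (15.0 - r).

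For d = 3: 1 - 2(2)/14.0 = 71% with r = 1, and 1 - 2(1.5)/13.5 = 78% with r = 1.5. For d = 8 and 8.75 the windows overlap or nearly meet, and the share was found by direct count.

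| Duration (months) | Never current at either interview |
|---|---|
| 2 | 86-93% |
| 3 | 71-78% |
| 4 | 57-63% |
| 6 | 29-33% |
| 8 | 0-4% |
| 8.75 (term) | 0% |

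The loss falls on pregnancies that end early. Term pregnancies could escape only near the window extremes: with a first gap of 10.0 months, those conceived in the first 10.0 - 8.75 = 1.25 months would be over by the interview.

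**4. What each source can supply.**

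| Pregnancy | Interview: occurrence | Interview: intention | Chart: occurrence | Chart: intention |
|---|---|---|---|---|
| Woman, current at interview | Yes | Yes | Possible | No |
| Woman, ended between interviews | No | No | Possible | No |
| Man's partner, current | Yes | Yes | No | No |
| Man's partner, ended between interviews | No | No | No | No |

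Enrolment is to be about half men, so the last two rows concern about 3600/2 = 1,800 participants.

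**5. Chart coverage.** Appendix P, item 8, looks back 6 months. The Data collection section says the review covers visits since the previous extraction. Taken literally, the form leaves 8.0 - 6 = 2.0 and 7.0 - 6 = 1.0 months uncovered.

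**6. Chart ascertainment by arm.** The HIV Prevention Interventions section trains intervention providers to assess pregnancy status at every visit. Comparison clinics continue usual care. A charted pregnancy may therefore be more likely to be recorded in the intervention arm.

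**The case against.** The strongest reply is that the interview is not the only source. Chart review records women's pregnancies visit by visit with a delivery date, and the Study instruments section says chart data cover the project year. A reader might infer that pregnancies ending between interviews are simply missed. For women the documents do not support that, because the chart can show them.

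A second reply is that P3f and P4f ask women who are not pregnant, at each interview, about wanting a pregnancy in the next 6 months. An analysis plan could pair that answer with a later charted pregnancy. This stands in part. But the protocol does not say it will be done, the 6-month horizon is shorter than the 7-8 month gaps, and a wish stated in advance is not the intention at conception that P12f asks about. Men's partners have no charted pregnancy to pair.

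Third, Appendix H is headed as the baseline form, so follow-up content is inferred. It does carry tick boxes for all three assessments, and the stated exceptions do not mention any added pregnancy item.

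Two stronger readings are tempting. One is a definite percentage of unintended pregnancies lost; the documents give neither pregnancy incidence nor how pregnancies end. The other is that the comparison is biased because the intervention alters how pregnancies end, or because ended pregnancies are mostly unintended. The protocol gives no data for either. Differential loss is a possibility only.

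**Conclusion.** The point holds in a limited form. Self-reported intention is collected only for pregnancies current at an interview, the chart form has no field for it, and pregnancies of men's partners have no second source. The chart's look-back is stated inconsistently, and its completeness may differ by arm.

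The loss is concentrated in pregnancies that end before the next interview. Under the assumptions shown it is large for those of 2-4 months and nil for term pregnancies at midpoint spacing. Its overall size cannot be derived from the documents. The outcome used for the power calculation, any unprotected sex in the past 3 months, is not touched. This is a worthwhile and cheap improvement to a listed outcome, not a threat to the trial's main conclusion.

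**What to change.** In the 6- and 12-month questionnaires, ask women, and men about their spouse or main partner, whether there has been any pregnancy since the last interview, including one that has ended. Record month and outcome, then use the existing P12f or P9m wording for each pregnancy. Define the outcome as any unintended pregnancy since baseline from this self-report, with the chart as a supporting source. Change the look-back in Appendix P, item 8, to run from the previous extraction, as the Data collection section already says.

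The cost is two or three questions, about one minute per interview, plus translation and an IRB amendment, before the 6-month round. Ended pregnancies may still be under-reported in a face-to-face interview, so the change narrows the gap and may not close it.

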**Write up to three method(s) from P6f:**

**Do not include female sterilization or male sterilization.**

|  | Method 1  ___ *-1. Don’t know*  ___ *-2. Refuse* | Method 2  ___ *-1. Don’t know*  ___ *-2. Refuse* | Method 3  ___ *-1. Don’t know*  ___ *-2. Refuse* |
| --- | --- | --- | --- |
| P8f. The last time you got *[insert method here]* who prescribed it to you or gave it to you?  SKIP THIS QUESTION IF METHOD IS LACTATIONAL AMENORRHEA, RHYTHM METHOD, OR WITHDRAWL | ___ 1. Someone in this  clinic  ___ 2. Someone in another  part of this health  facility  ___ 3. A provider at  another health  facility  ___ 4. Got method without  a prescription  ___ 5. Other source  (specify)  ________________  ___ *-1. Don’t know*  ___ *-2. Refused* | ___ 1. Someone in this  clinic  ___ 2. Someone in another  part of this health  facility  ___ 3. A provider at  another health  facility  ___ 4. Got method without  a prescription  ___ 5. Other source  (specify)  ________________  ___ *-1. Don’t know*  ___ *-2. Refused* | ___ 1. Someone in this  clinic  ___ 2. Someone in another  part of this health  facility  ___ 3. A provider at  another health  facility  ___ 4. Got method without  a prescription  ___ 5. Other source  (specify)  ________________  ___ *-1. Don’t know*  ___ *-2. Refused* |
| P9f. For how long have you been using *[insert method here]* now without stopping? | ________ [# of months]  ________ [# of years]  ___ *-1. Don’t know*  ___ *-2. Refused* | ________ [# of months]  ________ [# of years]  ___ *-1. Don’t know*  ___ *-2. Refused* | ________ [# of months]  ________ [# of years]  ___ *-1. Don’t know*  ___ *-2. Refused* |
| P10f. Does your spouse or main sex partner know that you are using this method of contraception? | _____ 0. No  _____ 1. Yes  _____ 2. Don’t have a spouse or main sex partner  ___ *-1. Don’t know*  ___ *-2. Refused* | _____ 0. No  _____ 1. Yes  _____ 2. Don’t have a spouse or main sex partner  ___ *-1. Don’t know*  ___ *-2. Refused* | _____ 0. No  _____ 1. Yes  _____ 2. Don’t have a spouse or main sex partner  ___ *-1. Don’t know*  ___ *-2. Refused* |

*[After answering, skip to P13f]*

P11f. How many months pregnant are you?

__________ # months pregnant

*_____-1. Don’t know*

*_____-2. Refused*

P12f. At the time you became pregnant, did you want to become pregnant *then*, did you want to wait until *later*, or did you *not want* to have any (more) children?

_____ 1. Then

_____ 2. Later

_____ 3. Not at all

*_____-1. Don’t know*

*_____-2. Refused*

P13f. In your relationship with your spouse or partner, who decides if or when you should have more children? *[Tick one.]*

_____ 1. I do

_____ 2. My partner does

_____ 3. We decide together

_____ 4. My extended family does

_____ 5. No one really decides, we just let whatever is going to

happen, happen

_____ 6. No opinion

_____ 7. Other (Specify) _____________________

*_____-1. Don’t know*

*_____-2. Refused*

P14f. In the past month, have you talked with your spouse or main partner about contraceptives or planning your family?

_____ 0. No

_____ 1. Yes

*_____-1. Don’t know*

*_____-2. Refused*

P15f. How confident are you that you could talk with your spouse or main partner in the next month about contraceptives or planning your family?

_____ 1. Very confident

_____ 2. Confident

_____ 3. Somewhat confident

_____ 4. Not at all confident

*_____-1. Don’t know*

*_____-2. Refused*

*[Skip items for men and go to Q1 in next section]*

